## Abstract

**Background:**

Ticagrelor monotherapy after 1–3 months of dual antiplatelet therapy (DAPT) has shown to be effective and safe after percutaneous coronary intervention (PCI), including in patients with an ST elevation myocardial infarction (STEMI). Direct omission of aspirin could further reduce bleeding complications and may reduce the incidence and expansion of intramyocardial haemorrhage (IMH), a frequent complication after revascularisation for a STEMI.

**Methods:**

This multicentre open label pilot study randomises 200 STEMI patients within 24 hours after primary PCI and before the first subsequent dose of aspirin to ticagrelor monotherapy or ticagrelor plus aspirin for twelve months. As IMH is more frequently observed after an anterior STEMI, IMH and infarct size will be determined with cardiac magnetic resonance (CMR) imaging in 60 anterior STEMI patients. In this subgroup, blood samples will be analysed for biochemical outcomes.

**Results:**

The primary safety endpoint consists of major adverse cardiac and cerebral events, and the primary efficacy endpoint is infarct size on CMR. Secondary efficacy endpoints consist of the incidence and extent of IMH determined by CMR, and of clinical bleeding events. Other endpoints include all-cause mortality and biochemical outcomes.

**Conclusion:**

The STOP-IMH pilot study compares ticagrelor monotherapy with ticagrelor plus aspirin directly after primary PCI in 200 STEMI patients. We aim to provide a signal of safety regarding ischemic events for the direct omission of aspirin after primary PCI, and to compare the infarct size by CMR between the two treatment strategies in the first week after primary PCI.

## Introduction

1

In patients with an ST-elevation myocardial infarction (STEMI), early mechanical reperfusion of the epicardial coronary artery by primary percutaneous coronary intervention (PCI) is recommended [1]. After a PCI, treatment with dual antiplatelet therapy (DAPT), consisting of aspirin and a P2Y12 inhibitor, is recommended to reduce ischemic complications of atherosclerotic disease and stent-related ischemic outcomes [1], [2]. The advent of the more potent P2Y12 inhibitors ticagrelor and prasugrel as well as ongoing improvements in stent technology, have led to a reduction of ischemic complications [3], which questions the additional benefit of aspirin. In addition, during past decade, the non-thrombotic pharmacologic treatment of cardiovascular disease has improved significantly [4], further influencing the balance of ischemic versus bleeding risk. To prevent unnecessary overexposure to antiplatelet therapy to reduce bleeding complications, it is pivotal to re-evaluate the post-PCI antiplatelet strategy over time. A novel strategy to reduce bleeding complications is the cessation of aspirin after 1 to 3 months with continuation of the P2Y12 inhibitor, which has been demonstrated to be safe regarding ischemic events and has showed a strong reduction in major bleeding events [5], [6], [7], [8], [9], [10], [11], [12]. These findings were confirmed in subgroup analyses of STEMI patient [13], [14].

As the majority of bleeding complications in the STEMI population occur during the first month [15], a cessation of aspirin directly after primary PCI, the aspirin-free strategy, could further reduce bleeding complications.

In addition to a reduction in clinical bleeding outcomes, ticagrelor monotherapy, compared to DAPT, may also limit the cardiac damage caused by reperfusion injury. Whereas ischemia causes limited damage to the coronary endothelium in the first hours after coronary arterial occlusion, reperfusion causes immediate endothelial cell injury, which can ultimately lead to microvascular injury (MVI). In the most extensive form, MVI can result in capillary destruction and, subsequently, intramyocardial haemorrhage (IMH) [16], [17]. External compression of the microvasculature by IMH increases vascular resistance which further impairs perfusion of the distal coronary microvasculature. Further damage is caused by the cytotoxic haem to which the cardiomyocytes are then exposed. It has been demonstrated that haemorrhagic myocardial infarctions are associated with up to 80% larger infarct sizes [18], and predicts major adverse cardiac events, adverse remodelling and reduced left ventricular function [19]. Therefore, reduction of haemorrhagic damage is a potential new target. A strong association of IMH with additional GPIIb/IIIa inhibitor treatment has been demonstrated, which corroborates the concept that more aggressive antithrombotic strategies after primary PCI might aggravate IMH [20]. Therefore, the choice of antiplatelet strategy after primary PCI for STEMI may be an important target influencing the occurrence and extent of IMH.

The efficacy and safety of direct omission of aspirin after PCI is currently being investigated in patients with an acute coronary syndrome (ACS) without ST-elevation [21], but has yet to be investigated in STEMI patients. The ongoing NEOMINDSET trial [22] investigates the effect of aspirin omission within four days (or later in case of a staged non-culprit PCI) after primary PCI in all ACS patients, including STEMI patients. As opposed to direct aspirin omission after primary PCI, this strategy possibly provides more protection for ischemic events in the acute phase, without a potential benefit on the reduction of IMH. As the ischemic risk is higher after a STEMI compared to other clinical settings in which patients undergo PCI [13], [14], [23], the STOP-IMH randomised trial was designed as a pilot study to provide a signal of safety regarding the incidence of ischemic events for the direct omission of aspirin after primary PCI with the continuation of ticagrelor monotherapy for 12 months compared to ticagrelor plus aspirin for 12 months in a relatively small number of STEMI patients.

Furthermore, we aim to assess the effect of this novel antiplatelet strategy on IMH and infarct size, as determined with CMR in a subgroup of patients with an anterior STEMI.

## Methods

2

### Design

2.1

The STOP-IMH pilot study is an open-label, prospective multicentre randomised clinical trial (RCT) in STEMI patients undergoing primary PCI, performed in the Netherlands. Fig. 1 presents a flow chart of the study design. Due to the pilot design, no formal power calculation has been performed. A total of 200 patients will be included and randomised within 24 h after the primary PCI and before the first dose of aspirin after primary PCI in a 1:1 ratio to ticagrelor monotherapy or ticagrelor plus aspirin for twelve months. In 60 patients with an anterior STEMI (due to a culprit in the left main (LM) artery or in the proximal- or mid left anterior descending (LAD) artery), CMR will be performed within 5 to 8 days post primary PCI. Randomisation is stratified for participation in the CMR subgroup and for participating centres.

**Fig. 1 f0005:**
[figure not shown]
Flowchart of the study design.

The Medical Ethics Committee reviewed and approved this study, and the study protocol conforms to the ethical guidelines of the 1975 Declaration of Helsinki [24]. This study is registered at ClinicalTrials.gov (NCT05986968).

### Study population

2.2

Patients aged 18 years or older are eligible for inclusion if a successful primary PCI (according to the treating physician) of the infarct-related vessel is performed with drug eluting stent placement for a clinically and electrocardiographically diagnosed STEMI. Criteria for STEMI consist of ≥0.1 mV elevation (of ≥0.2 mV in V2-V3) in two contiguous leads (in the absence of left ventricular (LV) hypertrophy or left bundle branch block (LBBB)) and reciprocal depressions. Patients will be excluded when they fulfil one of the following exclusion criteria: A known allergy or contraindication for aspirin, ticagrelor or prasugrel; a previous PCI or MI less than 12 months ago; previous cardiac surgery; pregnancy and breast feeding; concurrent use of oral anticoagulants; periprocedural use of GPIIb/IIIa inhibitors; planned surgical intervention within 12 months of PCI; creatinine clearance <30 mL/min or dialysis; PCI of stent thrombosis; suboptimal PCI result as judged by the treating interventional cardiologist; life expectancy shorter than 13 months.

### Treatment

2.3

As inclusion and randomisation takes place after the primary PCI, all patients receive loading dose aspirin and ticagrelor before primary PCI, as per local protocol. In the intervention arm, aspirin is discontinued directly after randomization and ticagrelor monotherapy (90 mg two times daily) is continued for 12 months. In specific cases, aspirin can be reinstated before 12 months after randomisation at the discretion of the treating physician, for example after a new ischemic event, such as a new myocardial infarction or stent thrombosis. In case of a staged PCI of non-culprit lesions, an additional loading dose of aspirin is administered prior to the staged PCI, after which the aspirin is discontinued.

In the control arm, patients will receive aspirin 75–100 mg once daily and ticagrelor 90 mg twice daily for 12 months. For several reasons, DAPT can be temporarily stopped and reinstated in the control arm at the treating physician’s discretion, such as surgery, an invasive procedure, or a clinically relevant bleeding. After 12 months, antiplatelet therapy in all patients is according to the treating physician.

If patients require treatment with an oral anticoagulant during the follow-up period, for example, in case of new-onset atrial fibrillation, ticagrelor will be switched to clopidogrel, and in the control arm, aspirin will be stopped. Other (non-coagulant) co-medication should be prescribed as recommended by the current international guidelines.

### CMR subgroup

2.4

Cardiac magnetic resonance (CMR) imaging provides noninvasively visualization of microvascular obstruction (MVO) (reflecting MVI) and IMH and relates this to the total infarct size and cardiac function [16], [25], [26]. Fig. 2 presents an example of IMH on CMR. Anterior infarct location is independently associated with the occurrence of IMH [20], [27] and with extensive IMH [20]. Therefore, CMR will be performed in patients with an anterior STEMI (LM or proximal or mid LAD culprit). We expect that this will be approximately 30% of the total population. Hence, 60 patients will be enrolled in the CMR subgroup. If 60 inclusions in the subgroup is reached before the total number of 200 patients have been included, the remaining anterior STEMI patients will be included as non-CMR patients. If the enrolment of subgroup patients has not yet reached 60 inclusions before the total of 200 will be enrolled, enrolment of the overall population will be stopped and only subgroup patients will be included. The timing of the CMR of 5 to 8 days after primary PCI is based on the expected expansion rate of IMH and differences in platelet aggregation between treatment groups. As both groups receive the loading dose of aspirin, no difference in platelet aggregation is expected in the first days after PCI. Thereafter, platelet inhibition will diverge between treatment groups. In the control group platelet inhibition will further increase by subsequent DAPT. In the experimental group the further inhibition of (newly formed) thrombocytes will rely on ticagrelor monotherapy. Results from earlier patient and animal studies demonstrated the greatest expansion of IMH within the first three days after primary PCI followed by a stable phase [18], [20], [28]. Decrease of IMH was demonstrated at ten days post PCI [28]. Therefore, CMR is preferably performed after several days to ensure the visibility of potential differences between treatments, but before resorption of the hematoma occurs. CMR examination will be performed on a 1.5 or 3.0-T clinical MRI scanner using a phased array cardiac receiver coil. All images are ECG-gated and acquired during mild end-expiration breath holding.

**Fig. 2 f0010:**
[figure not shown]
CMR images of intramyocardial haemorrhage. CMR images of a patient with an acute anteroseptal infarction with IMH. Cine showing anteroseptal akinesia, indicated by the white arrows (A). Black arrows indicate IMH in the T2 map and T1 map (B, C). White arrows indicate IMH as a hypointense core within a hyperintense area in the T2W STIR and T2* map (D, E). LGE demonstrating MVO, indicated by the white arrows. The white Asterix shows normal myocardium (F). CMR: cardiac magnetic resonance, IMH: intramyocardial haemorrhage, T2W STIR: T2-weighted short-tau inversion recovery, LGE: late gadolinium enhancement, MVO: microvascular obstruction.

Steady-state free-precession cine imaging is used to measure LV volumes and calculate LV ejection fraction (LVEF) and to assess left ventricular segmental and global strain. T2-weighted imaging, T2 mapping and T2* mapping will be acquired in short axis planes for the detection of intramyocardial haemorrhage and infarct-related oedema. T1 maps (native and post contrast) will be acquired to quantify remote myocardial inflammation. Finally, after the administration of a gadolinium-based contrast agent (0.1 mmol/kg), LGE imaging will be performed to determine total infarct size, the transmural extent of infarction and presence and extent of microvascular obstruction.

Blood plasma samples of patients within the CMR subgroup will be stored on the day of the randomisation, the day of the CMR and during two outpatient visits (after 6 weeks and after one year) for future analyses regarding inflammatory- and coagulation response, unless logistically not feasible. Furthermore, in the CMR subgroup platelet inhibition by aspirin will be measured using VerifyNow on the day of randomisation, 2–4 days after primary PCI and on the day of the CMR, to compare the decrease of platelet inhibition by aspirin within the first week between patients receiving only the loading dose and patients in which the aspirin is continued. The VerifyNow aspirin assay measures platelet aggregation using fibrinogen and arachidonic acid. When platelets are not inhibited by aspirin, they bind to the fibrinogen on activation by the arachidonic acid. This results in agglutination of the fibrinogen, which is measured in Aspirin Reaction Units (ARU).

### Follow-up and outcomes

2.5

Our primary safety endpoint is the composite of major adverse cardiac and cerebral events (MACCE) consisting of myocardial infarction, stent thrombosis, ischemic stroke and cardiovascular mortality.

The primary efficacy endpoint is the infarct size, determined by CMR on days 5 to 8 after primary PCI.

Secondary efficacy endpoints consist of the incidence and extent of IMH determined by CMR, and of clinical bleeding events. Bleeding events are defined according to the Bleeding Academic Research Consortium (BARC) criteria. BARC type 2 or higher bleeding events are collected. Other endpoints include all-cause mortality, echocardiographic left ventricular function between 6 and 13-months follow-up, and biochemical outcomes such as platelet inhibition to aspirin, inflammatory response and coagulation markers. Complications and adherence to medication during follow-up is retrieved by telephonic follow-up consults at one, three and thirteen months post primary PCI.

### Data collection

2.6

Data are collected in a pseudonymised manner in Castor electronic data capture (EDC) [29]. Medical history, baseline characteristics, procedural characteristics and medication at discharge will be retrieved from the patient’s electronical health record (EHR). Complications and medication changes reported by the patients during telephonic follow-up visits will be verified in the EHR and registered in the electronic Clinical Research Form (eCRF) of Castor EDC. Changes in the antiplatelet regimen reported by the patient will be verified in the EHR, and the details about the date, duration and reason for temporary or permanent interruption or reinstatement of aspirin will be documented in the eCRF. Diagnostic imaging and biochemical results are also registered in Castor EDC.

### Data protection and quality control

2.7

Two times per year, external monitoring will take place at each site to ensure completeness and correctness of data in the eCRF. Before the data analysis, a clinical event committee (CEC) will evaluate all endpoints to ensure the correctness of the registered complications. Each site creates and stores an identification log which is securely stored at the specific site to identify the patient to the Castor identification number if required. All study data will be stored for 25 years after the last follow-up visit.

### Safety of study participants

2.8

A data safety monitoring board (DSMB) was installed to ensure safety of the study participants. The DSMB will periodically review the study’s safety outcomes. If three stent thromboses have occurred in the experimental arm, an interim safety analysis will be performed.

### Statistical analysis

2.10

Statistical analyses will be conducted according to both the intention to treat and the per protocol principles. The main analysis will be based on the intention to treat principle. Continuous baseline demographic and clinical variables will be expressed as mean ± standard deviation (SD) for normally distributed continuous parameters, and as median (IQR) for those with a skewed distribution. Categorical data will be expressed as frequencies and proportions. For continuous non-normally distributed variables we will use the Mann-Whitney *U* test. For continuous normally distributed variables, we will use the unpaired *t*-test. Cox regression analysis will be performed to calculate the hazard ratio’s and concomitant confidence intervals to compare outcomes between treatment strategies. Risk differences between treatments will also be calculated. The main analyses will comprise of clinical outcomes in the first three months after primary PCI and of CMR results. In addition, we will report on clinical outcomes at thirteen months.

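### Infarct size in 60 CMR patients is to be compared by an unadjusted t-test or Mann-Whitney test chosen by distribution; one pre-specified adjusted model would be more precise at almost no cost

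*Protocol article*

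**What the plan says.** Section 2.5 (Follow-up and outcomes) defines the endpoint: "The primary efficacy endpoint is the infarct size, determined by CMR on days 5 to 8 after primary PCI". Section 2.4 (CMR subgroup) sets its sample: "Hence, 60 patients will be enrolled in the CMR subgroup".

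Section 2.10 (Statistical analysis) gives two rules for continuous variables: "For continuous non-normally distributed variables we will use the Mann-Whitney" U test, and "For continuous normally distributed variables, we will use the unpaired" t-test. It lists CMR results among the main analyses. It names no covariate, centre term or stratified test, and no criterion for deciding that a variable is normally distributed. It mentions confidence intervals only with the Cox hazard ratios.

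Section 2.1 (Design) says: "Randomisation is stratified for participation in the CMR subgroup and for participating centres". Section 2.6 (Data collection) provides for medical history, baseline characteristics and procedural characteristics. The culprit segment (left main, proximal LAD or mid LAD) is known for every CMR patient, because it defines eligibility for the subgroup. For the aspirin-response outcome, section 2.4 adds that "platelet inhibition by aspirin will be measured using VerifyNow on the day of randomisation", on days 2–4 and on the CMR day.

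**The concern.** Infarct size is continuous and no other method is given for it, so the two tests in section 2.10 govern the primary efficacy result. Two things follow.

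First, prognostic information that is already recorded goes unused. Section 3.2 (Weaknesses) calls underpowering the main limitation, and section 2.1 says that no formal power calculation was made. Precision that can be recovered without extra patients therefore matters more here than usual.

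Second, the look of the observed distribution decides what is estimated. If infarct size seems normal, the result is a comparison of means. If it seems skewed, the result is a rank test, which does not itself give a mean difference with an interval. Section 3.1 (Strengths) expects the results to enable later powered studies, and planning those needs a difference and a standard deviation.

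**Working it through.** **Inputs from the protocol article.** N = 60 (section 2.4) and 1:1 allocation (section 2.1), so 30 per arm. The 60 comes only from the expected anterior share: 0.30 × 200 = 60. The article states no power, effect size or SD, so there is no figure of its own to reproduce.

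**Assumed inputs.** Two-sided 5% level, 80% power, SD = 1, no dropout. R², the share of outcome variance that the covariates explain, is not in the article and is varied from 0 to 0.4.

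**Step 1: unadjusted benchmark.** The detectable difference is (1.960 + 0.842) × √(2/30) = 0.72 SD by the normal approximation, or 0.74 SD by the exact t calculation. Power for a true difference of 0.5 SD is 48% (t).

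**Step 2: adjusted model.** With p covariates, the variance of the treatment difference relative to the t-test is

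(1 − R²) × (1 + p/(N − p − 3)).

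The second term is the cost in degrees of freedom. For p = 3 it is 1 + 3/54 = 1.056. The interval width changes by the square root of the factor, and the t quantile adds about 0.1%. The equivalent number of unadjusted patients is 60 divided by the factor.

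| R² (assumed) | Variance factor | Interval width | Equivalent N | Detectable difference (SD) | Power at 0.5 SD |
|---|---|---|---|---|---|
| 0 | 1.056 | ×1.03 | 57 | 0.76 | 46% |
| 0.1 | 0.950 | ×0.98 | 63 | 0.72 | 50% |
| 0.2 | 0.844 | ×0.92 | 71 | 0.68 | 54% |
| 0.3 | 0.739 | ×0.86 | 81 | 0.63 | 60% |
| 0.4 | 0.633 | ×0.80 | 95 | 0.59 | 67% |

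More parameters cost more. With p = 5, R² of 0.2, 0.3 and 0.4 gives widths of ×0.94, ×0.88 and ×0.81.

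**Step 3: centre alone.** CMR participation is a stratification factor but is constant within the 60 patients, so only centre remains. Centre-stratified randomisation was simulated with 3, 5, 6 and 10 equal centres, 1,500 runs per setting. The number of centres is not in the article.

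- Intraclass correlation 0: adjusting for centre left the standard error unchanged.
- Intraclass correlation 0.05: it fell by about 2% (for example 0.255 to 0.250).
- Intraclass correlation 0.10: it fell by about 4–5% (for example 0.254 to 0.244).

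In these balanced designs the actual spread of the estimate was the same with and without the centre term. The gain is that the reported standard error stops being slightly too large.

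**Step 4: validity.** Type I error of the unadjusted t-test in the same runs was 3.4–6.1% across settings. The simulation error is √(0.05 × 0.95/1,500) ≈ 0.6 percentage points. Rates tended to fall below 5% when centre effects were present. The test is therefore valid and at most mildly conservative.

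**Step 5: choice of test.** The two rules in section 2.10 are exclusive, and the distribution decides between them. The quantity reported for the primary efficacy endpoint is thus not fixed before the data are seen.

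**The case against.** The strongest reply is that a journal article condenses the plan. The test sentences are generic, never mention infarct size by name and do not rule out adjustment, so a full analysis plan may already contain an adjusted model. That limits how confident one can be. It does not remove the point, because the article goes beyond silence: it names specific tests and places CMR results among the main analyses.

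The reply also holds that nothing is invalid, and that stands. An unadjusted comparison in a 1:1 randomised trial is unbiased. A reader might infer from the ignored strata that the test misses its nominal level badly. That would need centre to explain a large share of infarct-size variance, and no figure in the article supports this. Nor are both strata lost, since CMR participation does not vary within the 60.

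Other stronger readings also lack support:

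- Section 2.4 says that "CMR examination will be performed on a 1.5 or 3.0-T clinical MRI scanner", but not that field strength differs by centre, so centre cannot be taken as a proxy for it.
- Nothing says that aspirin reaction units or plasma markers predict infarct size.
- Infarct size has no pre-treatment value, so adjustment here means baseline covariates.
- No normality test is named, so the chance of ending with the rank test cannot be calculated from the plan.
- Choosing a rank test does not prevent reporting means, SDs or a location-shift interval. The information for a later trial is not lost, only not promised.
- Stratifying the Cox model is tempting, but no gain from it has been shown.

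Finally, the gain is not free. With weak covariates it is near zero or slightly negative.

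**Conclusion.** The point holds as a cheap improvement, not as an error of validity. The stated analysis of the primary efficacy endpoint omits centre and the recorded baseline and procedural data, and leaves the estimated quantity to the observed distribution.

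If three covariates explain 20–40% of the variance, adjustment narrows the interval by about 8–20%, equivalent to 11–35 more unadjusted patients. At 10% the gain is about 2%, and at zero the loss is about 3%. Most of any gain comes from the covariates and little from centre. All of this rests on assumed R² values, 30 patients per arm and complete data. The case for fixing a single estimator in advance does not depend on R².

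**What to change.** Before analysis, specify one linear model for infarct size, to be used whatever the observed distribution:

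- treatment;
- centre, with small centres pooled or centre as a random effect;
- two or three pre-randomisation covariates already recorded, such as culprit segment, plus an ischaemic-time variable if it is among the recorded procedural characteristics. The article does not name one, so the sponsor should confirm it.

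Report the adjusted mean difference with a robust 95% confidence interval, and keep Mann-Whitney as a sensitivity analysis. Analyse the later aspirin reaction units by ANCOVA on the randomisation-day value where that sample precedes the first aspirin dose after PCI. The article places the sample on the day of randomisation without saying that it does.

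The cost is a change of wording and a few degrees of freedom. Culprit segment at three levels uses two parameters, and centre uses one fewer than the number of pooled groups if fitted as a fixed effect, so the model should stay small. No new data are needed if the chosen covariates are confirmed as recorded.
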